## Abstract

**Background:**

Probucol, a cholesterol-lowering agent that paradoxically also lowers high-density lipoprotein cholesterol has been shown to prevent progression of atherosclerosis. The antiplatelet agent cilostazol, which has diverse antiatherogenic properties, has also been shown to reduce restenosis in previous clinical trials. Recent experimental studies have suggested potential synergy between probucol and cilostazol in preventing atherosclerosis, possibly by suppressing inflammatory reactions and promoting cholesterol efflux.

**Methods/design:**

The Synergistic Effect of combination therapy with Cilostazol and probUcol on plaque stabilization and lesion REgression (SECURE) study is designed as a double-blind, randomised, controlled, multicenter clinical trial to investigate the effect of cilostazol and probucol combination therapy on plaque volume and composition in comparison with cilostazol monotherapy using intravascular ultrasound and Virtual Histology. The primary end point is the change in the plaque volume of index intermediate lesions between baseline and 9-month follow-up. Secondary endpoints include change in plaque composition, neointimal growth after implantation of stents at percutaneous coronary intervention target lesions, and serum levels of lipid components and biomarkers related to atherosclerosis and inflammation. A total of 118 patients will be included in the study.

**Discussion:**

The SECURE study will deliver important information on the effects of combination therapy on lipid composition and biomarkers related to atherosclerosis, thereby providing insight into the mechanisms underlying the prevention of atherosclerosis progression by cilostazol and probucol.

**Trial registration number:**

ClinicalTrials (NCT): NCT01031667

## Background

The benefit of reducing low-density lipoprotein (LDL) cholesterol in the management of coronary artery disease (CAD) has been demonstrated in various large-scale randomized clinical trials [1]. These trials have shown that statin therapy, which is currently considered an essential element in CAD treatment regimens, does improve clinical outcomes, but is only able to prevent coronary events in less than 30% of patients. Therefore, a need remains for new and more effective cardiovascular drug therapies.

Probucol, a mild cholesterol-lowering agent with antioxidant and anti-inflammatory properties, has been shown to reduce atherosclerosis and prevent restenosis after percutaneous coronary intervention (PCI) [2]. However, probucol also causes a remarkable reduction in high density lipoprotein (HDL) and prolongation of QT intervals on electrocardiograms, side effects that have led to the withdrawal of probucol from the market in many countries. Although the mechanisms underlying the antiatherosclerotic effect of probucol remain unclear, previous speculation has centered on inhibition of oxidative modification of LDL cholesterol [3]. However, recent studies have suggested that enhanced reverse cholesterol transport caused by activation of cholesteryl ester transfer protein (CETP) and scavenger reverse cholesterol class B type 1 (SR-B1) is the major mechanism responsible for both the antiatherogenic effect and reduction of HDL levels by probucol [4-6]. The apparent lowering of HDL levels by probucol may be related to a change in the composition of HDL subtypes, including an increase in preβ1-HDL ("lipid-poor" apoA-1), that participate in the cholesterol efflux [7]. Therefore, the lowering of HDL by probucol is not a side effect, per se, but instead may reflect its main effect of increasing cholesterol efflux. Furthermore, probucol has been shown to inhibit mononuclear cell adhesion and reduce expression of vascular cell adhesion molecule (VCAM) [8]. Probucol also promotes nitric oxide-mediated vasodilatation and re-endothelialization, and inhibits smooth muscle cell proliferation [9].

Cilostazol, an inhibitor of type 3 phosphodiesterase that exerts antiplatelet activity through suppression of cyclic adenosine monophosphate degradation [10], also exhibits diverse antiatherogenic properties. Studies have shown that cilostazol improves endothelial function by increasing nitric oxide production [11], promotes scavenging of free radicals [12], and inhibits foam cell formation [13] and smooth muscle cell proliferation [14]. In addition, cilostazol has been shown to decrease triglyceride concentrations and increase HDL cholesterol concentration, possibly by increasing the activity of lipoprotein lipase [15,16].

A previous study by Sekiya et al. [17] reported that cilostazol and probucol combination therapy reduced restenosis after stent implantation more effectively than did either cilostazol or probucol alone. In addition, recent studies have demonstrated potential synergistic effects of cilostazol and probucol used in combination in the prevention of atherosclerosis [18,19]. Yoshikawa et al. [18] found that combined administration of cilostazol and probucol induced a greater decrease in the atherosclerotic lesion area in LDL receptor-deficient mice than did administration of each drug separately. Park et al. [19] showed that cilostazol and probucol combination therapy inhibited the expression of VCAM-1 and monocyte chemoattractant protein-1 (MCP-1) more effectively than did either cilostazol or probucol monotherapy.

Intravascular ultrasound (IVUS) is a useful imaging modality for assessment of atherosclerotic plaque and vessel wall morphology. Especially, Virtual histology (VH) IVUS (Volcano Therapeutics, Inc., Rancho Cordova, California) using spectral analysis of the radiofrequency ultrasound back-scatter signals allows identification and relative quantification of four different components of atherosclerotic plaques: fibrous, fibro-fatty, dense calcium and necrotic core [20-25]. Therefore, the SECURE study is designed to investigate effects of cilostazol and probucol combination therapy on coronary plaque volume and composition using VH-IVUS in comparison with cilostazol monotherapy.

## Methods/design

### Study Design

This is a double-blind, placebo-controlled, randomised, multicenter clinical trial to evaluate the efficacy of probucol and cilostazol combination therapy compared with cilostazol alone in the prevention of coronary plaque progression (Figure 1). A total of 118 patients (see Sample size calculation, below) will be enrolled at five PCI centers in Korea. After enrollment and baseline investigation with IVUS and VH to establish index non-PCI target intermediate lesions and stented PCI target lesions, patients will be evaluated in clinical follow-up visits at 1, 3, 6, and 9 months. In the final 9-month follow-up examination, patients will be evaluated by IVUS and VH to assess plaque volume and plaque composition in index non-PCI target intermediate lesions, and measure neointimal hyperplasia in index stented PCI target lesions. Lipid profiles, to include total cholesterol, LDL, HDL, triglyceride, apolipoprotein A-1 and B, LDL particle size and HDL subfractions, and biomarkers associated with atherosclerosis, including high-sensitivity C-reactive protein (hsCRP), oxidized LDL, VCAM-1, von Willebrand factor (vWF) and lipoprotein (a) [Lp(a)], will be measured at enrollment, and at 1- and 9-month follow-up examinations. The trial algorithm is shown in Figure 1. This is an investigator-initiated clinical trial with grant support from Korea Otska Pharmaceutical Co. Ltd (Seoul, Korea). Other than providing financial support, the company is not involved in developing study protocols or study processes, including site selection, management, and data collection and analysis. The study is performed according to the principles of the Declaration of Helsinki and according to common guidelines for clinical trials (ICH-GCP). The authors are solely responsible for the design and editing of this paper and its final content. The trial protocol has been approved by the local institutional review boards of each patient-enrolling center, and has been registered at http://www.clinicaltrials.gov (NCT01031667). Patient information, blood samples, and IVUS, VH and coronary angiogram images will be coded with the identification number of this study; investigators are blinded to patient identifying information, which has been replaced with a coded number.

**Figure 1 F1:**
[figure not shown]
**SECURE study algorithm**. PCI, percutaneous coronary intervention; DM, diabetes mellitus; VH-IVUS, Virtual Histology intravascular ultrasound; MI, myocardial infarction; TVR, target vessel revascularization; LDL, low-density lipoprotein; HDL, high-density lipoprotein; hsCRP, high-sensitivity C-reactive protein; VCAM-1, vascular cell adhesion molecule-1; Lp(a), lipoprotein (a); vWF, von Willebrand factor.

### Study population and Randomisation

Patients more than 20 years of age who have had at least one significant coronary artery stenosis requiring PCI with stent implantation and one intermediate lesion on a native coronary artery with luminal narrowing of ≥ 30% and ≤ 70% by visual estimation, and who also meet all inclusion and exclusion criteria (Table 1) are eligible for this study. Those who agree to participate in the study and give written consent are randomised (1:1) to either cilostazol and probucol combination therapy or cilostazol monotherapy (control) using a web-based online randomization system. The randomization is stratified by enrolling site and the presence of diabetes in order to ensure an even distribution between the two groups of major factors that might contribute to the primary end point. After enrollment, all patients will receive a starting dose of 20 mg simvastatin. The dose of simvastatin will be adjusted to reach a target LDL level of < 100 mg/dL. Concomitant use of other drugs that interfere with serum lipid levels, such as niacin, CETP or lipoprotein-associated phospholipase A2 (Lp-PLA2) inhibitor, fenofibrate or omega-3, is not allowed.

**Table 1 T1:** Patient Inclusion and Exclusion Criteria

Inclusion criteria
1. Male or female over 20 years of age
2. Clinical indication for coronary angiography
3. Presence of at least one significant coronary artery stenosis (>50%) requiring PCI with stent implantation and one intermediate lesion with luminal narrowing of ≥30% and <70% by visual estimation on native coronary arteries.
4. Presence of at least one PCI target lesion (reference diameter 2.5~4 mm, lesion length ≤26 mm) with >50% diameter stenosis that can be covered with a single Zotrolimus-eluting stent (Endeavor Sprint, Medtronic Vascular Inc, Santa Rosa, CA).
5. Able to understand and willing to provide written informed consent
Exclusion criteria
1. Intermediate lesions that might provide difficulty for IVUS evaluation because of following reasons: heavy calcification (>90° Arc), tortuous vessel with severe angulation, total occlusion, or bifurcation lesions
2. Previous PCI in the last 6 months
3. Previous coronary artery bypass graft
4. Patients with AMI undergoing primary PCI or rescue PCI after thrombolysis
5. Cardiogenic shock
6. Inability to take adequate antiplatelet therapy (aspirin and clopidogrel)
7. Thrombocytopenia (platelet count <70 × 10^9^/l)
8. Known hypersensitivity or contraindication to any of the following medications: Heparin, aspirin, clopidogrel, cilostazol, probucol, statin, contrast media
9. History of severe ventricular arrhythmia
10. Significant QTc prolongation (≥470 ms) on electrocardiogram
11. Heart failure (New York Heart Association class III/IV) or left ventricular ejection fraction ≤35%
12. Familial hypercholesterolemia
13. Uncontrolled hypertriglyceridemia (>400 mg/dL)
14. Chronic renal failure with serum creatinine level ≥2 mg/dL
15. Severe liver disease or transaminase level ≥3 times the upper limit of normal.
16. Pregnancy or women at age of childbearing potential

An additional file "Figure 1" contains figure 1.

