### Statistical considerations

#### Sample size calculation

The calculation of the sample size was based on an in-equality design and a two-sample, two-sided test. Assuming a standard deviation of 8%, an α-level of 0.05 and a statistical power of 80%, 41 patients are required for each group (combination therapy, cilostazol monotherapy) to demonstrate a 5% difference in the mean plaque volume in a 10-mm segment with the greatest disease severity of the index intermediate lesion. Making allowance for a drop-out rate of 30% increases the number of patients required for each group to 59. The treatment difference and standard deviation assumptions are based on previous clinical and animal studies. Several IVUS studies have successfully demonstrated the effect of statins in reducing plaque volume. Yokoyama et al. [22] showed a 3.2% reduction in plaque volume in patients treated with atorvastatin (10 mg/day) for 6 months. The ASTEROID trial achieved about a 25% reduction in the normalized total atheroma volume using rosuvastatin (40 mg/day) for 24 months [28]. Recently, Tardif at al. [29] reported that a 12-month therapy with succinobucol, an analog of probucol, reduced the plaque volume of index lesions by 1.5%, whereas the control group showed no significant change in plaque volume. Notably, the results of an animal study evaluating the antiatherogenic effects of cilostazol and probucol showed that combination therapy was more effective in reducing the size of atherosclerotic lesions than was administration of either drug alone [18]. For this reason, we expect that cilostazol and probucol combination therapy will be more potent in reducing plaque volume than succinobucol, and hypothesize that the combination therapy could achieve a reduction in plaque volume 5% greater than that achieved by cilostazol monotherapy.

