### Statistical analysis

All statistical analyses will be carried out by an independent organization, ADM Korea Inc. All primary and secondary end points will be analyzed on a modified intention-to-treat basis (all randomized subjects who receive at least one dose of study drug and have IVUS and VH measurements at baseline and at the study end point). The primary efficacy analysis will be performed using an analysis of covariance model, adjusting for baseline values. If the data are not distributed normally, a nonparametric analysis of covariance analysis will be used. All continuous secondary efficacy variables will be analyzed using similar methods. The composite end point of cardiovascular events will be analyzed by comparing Kaplan-Meier event rates using a log-rank test. Independent predictors of major adverse cardiac events (MACE) were determined using a multiple logistic regression analysis.

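### Baseline LDL can mix statin-treated and untreated levels; adding statin use at enrolment to the lipid ANCOVA would recover some precision on secondary end points

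*Protocol article*

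**What the plan says.** Study Design places the lipid and biomarker samples at enrolment, 1 month and 9 months. Study population and Randomisation then says: "After enrollment, all patients will receive a starting dose of 20 mg simvastatin". The dose is afterwards adjusted in both arms towards an LDL below 100 mg/dL. The same section also bars other lipid-modifying medication alongside the study treatment; it gives no lead-in period for that ban.

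Table 1 mentions statins, probucol and cilostazol only under hypersensitivity or contraindication. It contains no requirement for statin-naive status, a stable earlier dose, a run-in or a washout. Randomisation is stratified by site and diabetes, not by earlier lipid treatment.

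On analysis, the Statistical analysis section says: "The primary efficacy analysis will be performed using an analysis of covariance model, adjusting for baseline values". For lipids and the other continuous secondary measures: "All continuous secondary efficacy variables will be analyzed using similar methods".

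**The concern.** Take two patients with the same enrolment LDL, one never treated with a statin and one already on one. The first patient's 1-month value includes a first statin response. The second patient's reflects a switch or a continuation. Their expected follow-up values differ, but a model with baseline LDL as its only covariate predicts the same value for both. The difference goes into the error term.

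Two things are at stake. The between-arm lipid estimates are less precise than they could be, and a chance imbalance in earlier statin use is not adjusted for. Also, a within-arm change from baseline partly describes the move onto simvastatin rather than the study drugs. The Discussion calls lipid change a further focus of the trial, so these end points carry some weight even though they are secondary.

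**Working it through.** **1. The plan's own figure.** Inputs are from Sample size calculation: "Assuming a standard deviation of 8%, an α-level of 0.05 and a statistical power of 80%, 41 patients are required for each group", two-sided, for a 5% difference.

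n = 2 × [8 × (1.960 + 0.842) / 5]² = 40.19, so 41 per group. With 30% drop-out, 41 / 0.70 = 58.6, so 59 per group and 118 in total. The stated figures reproduce. The calculation is a plain two-sample one that takes no credit for baseline adjustment, so a weaker covariate does not undercut it.

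**2. Primary end point.** Suppose a share p is already on a statin and the lesions of untreated patients shrink by an extra 3.2%, the 6-month atorvastatin effect cited in the article. Then SD = √[8² + p(1 − p) × 3.2²].

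- p = 0.2: √65.64 = 8.10%; n = 41.2, so 42 per group; power at 41 is 79.8%.
- p = 0.5: √66.56 = 8.16%; n = 41.8, so 42 per group; power at 41 is 79.2%.

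Power at 41 with SD 8% is 80.8% on the same normal approximation. With an assumed between-patient coefficient of variation of 30-40%, the simulated correlation between baseline and 9-month plaque volume is 0.96-0.98 whether 0%, 30% or 50% are pre-treated. The baseline covariate loses essentially nothing here.

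**3. LDL.** The article gives no LDL distribution, statin response or share pre-treated, so all of these are assumptions:

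- Untreated LDL U has mean 130 and SD 32 mg/dL.
- A statin multiplies U by a factor with mean 0.65 or 0.75 and SD 0.08.
- Baseline is the multiplied value if the patient is on a statin, otherwise U. Follow-up is a multiplied value for everyone.
- Independent within-person noise of SD 0, 10 or 20 mg/dL is added at each visit.

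Follow-up was regressed on baseline alone, then on baseline plus a statin indicator (400,000 simulated patients per cell). Ratio of the second residual variance to the first:

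| Multiplier | Noise SD | 10% on statin | 20% | 40% | 60% |
|---|---|---|---|---|---|
| 0.65 | 0 | 0.65 | 0.55 | 0.51 | 0.53 |
| 0.65 | 10 | 0.82 | 0.75 | 0.71 | 0.72 |
| 0.65 | 20 | 0.95 | 0.92 | 0.90 | 0.91 |
| 0.75 | 10 | 0.87 | 0.81 | 0.76 | 0.77 |
| 0.75 | 20 | 0.96 | 0.94 | 0.92 | 0.93 |

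Without noise and with multiplier 0.65, mean change is about −45 mg/dL in untreated patients (130 × 0.65 − 130 = −45.5) and about 0 in those already treated. A simple titration step for readings of 100 mg/dL or more moves the ratios by only about 0.01-0.02.

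A ratio of 0.71 shortens a confidence interval by 16% (√0.71 = 0.84); a ratio of 0.96 shortens it by 2% (√0.96 = 0.98).

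**4. Cross-check.** A second model fixes the baseline to follow-up correlation among all-untreated patients at 0.5 or 0.7 and lets the earlier statin lower baseline LDL by 20-40%. With 50% pre-treated, a 30% statin effect and correlation 0.7, the unexplained share of variance is 0.70 without the indicator and 0.53 with it, against 0.51 if everyone were untreated. The ratio is 0.525 / 0.696 = 0.75, inside the range above.

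**5. Validity.** With 41 per arm and 50% pre-treated, the ANCOVA on baseline alone has a simulated type I error of 0.047 and a bias of 0.04 mg/dL (Monte Carlo SE 0.06). With 40% pre-treated, the between-arm difference in earlier statin use has SD √(2 × 0.4 × 0.6 / 41) = 0.108, about 11 percentage points. This adds noise, not bias.

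**The case against.** The strongest reply is that the article is a condensed account. It never says that patients are on statins at enrolment, nor how many. Rules on earlier treatment may sit in the full protocol, medication history is probably collected anyway, and further covariates are commonly left to an analysis plan. ANCOVA on baseline is a standard and valid model. This stands in large part, and it is why the point is an improvement to the stated model rather than an error. It does not remove the point: the article prints its eligibility list, its sampling times and its covariate, and together these allow a mixed LDL baseline that the stated model ignores.

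A reader might also infer more than the article supports:

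- **That the lipid sample is nearly doubled.** A residual variance of about half arises only in a model in which LDL has no within-person variation. With noise the gain is much smaller.
- **That all biomarkers are affected.** Only LDL was modelled. Extension to total cholesterol and apolipoprotein B is by analogy. The article gives no basis for a comparable statin shift in HDL and its subfractions, Lp(a), VCAM-1 or von Willebrand factor.
- **That earlier users of probucol or cilostazol must be excluded.** This rests only on silence in a condensed text and would set an eligibility rule. It is not part of this point.

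**Conclusion.** The point holds as a modest loss of precision on statin-sensitive lipid end points: LDL, with total cholesterol and apolipoprotein B. Adding statin use at enrolment would lower the LDL residual variance by roughly 5-30% if within-person SD is 10-20 mg/dL and 10-60% of patients are already treated. About 50% is an upper limit that ignores visit-to-visit noise. If hardly any patients are on a statin at enrolment, the gain is close to nil.

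Two stronger conclusions do not follow. The between-arm comparison is not biased, because randomisation protects it. Nor is the primary analysis or the sample size weakened in any material way: baseline plaque volume remains a strong predictor, and the article's own statin effect adds one patient per group before drop-out.

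**What to change.** Pre-specify statin use at enrolment (yes/no, from the medication history) as an additional covariate in the ANCOVA for LDL, total cholesterol and apolipoprotein B. State that conclusions on these end points rest on the between-arm difference, and that within-arm change from baseline is descriptive because it can include a change of background statin.

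The cost is one degree of freedom per model and one binary variable, which may already be collected. If the full protocol or the analysis plan already does this, a sentence pointing to it is enough. The plaque-volume model, the sample size and the eligibility criteria need no change on this account.

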### Index intermediate lesion for evaluating plaque volume

An intermediate lesion is defined as a lesion with a luminal narrowing ≥ 30% and ≤ 70% (estimated visually) that does not require percutaneous coronary intervention. One such lesion located in the proximal or mid segment of coronary arteries is selected by the operator as the index intermediate lesion. Intermediate lesions that might prove difficult to evaluate by IVUS, such as bifurcating lesions, heavily calcified lesions (> 90° arc), and those in tortuous vessels with severe angulation are avoided in the selection of an index lesion.

### Percutaneous coronary intervention

All patients should be on chronic aspirin (100-325 mg/day) and clopidogrel (75 mg/day) therapy for ≥ 5 days or receive aspirin (250 mg) and clopidogrel (300-600 mg) loading at least 12 hours before PCI. Unfractionated heparin will be administered according to local standards of care (target ACT 250 sec) at a dosage as per label instructions. The use of glycoprotein IIb/IIIa inhibitors will be left to the discretion of the operator. The criteria for an index PCI target lesion are a stenotic lesion with a stenosis diameter > 50% and lesion length ≤ 26 mm that can be covered by a single stent. All PCI target lesions, including additional lesions not established as index lesions, will be treated with Zotarolimus-eluting stents (Endeavor Sprint, Medtronic Vascular Inc, Santa Rosa, CA). After implantation of stents, aspirin (100 mg/day) and clopidogrel (75 mg/day) will be administered during the period of study.

